## Abstract

**Background:**

Impairment in social functioning is a key component of personality disorder. Therefore psycho-education and problem solving (PEPS) therapy may benefit people with this disorder. Psycho-education aims to educate, build rapport, and motivate people for problem solving therapy. Problem solving therapy aims to help clients solve interpersonal problems positively and rationally, thereby improving social functioning and reducing distress. PEPS therapy has been evaluated with community adults with personality disorder in an exploratory trial. At the end of treatment, compared to a wait-list control group, those treated with PEPS therapy showed better social functioning, as measured by the Social Functioning Questionnaire (SFQ). A definitive evaluation is now being conducted to determine whether PEPS therapy is a clinically and cost-effective treatment for people with personality disorder

**Methods:**

This is a pragmatic, two-arm, multi-centre, parallel, randomised controlled clinical trial. The target population is community-dwelling adults with one or more personality disorder, as identified by the International Personality Disorder Examination (IPDE). Inclusion criteria are: Living in the community (including residential or supported care settings); presence of one or more personality disorder; aged 18 or over; proficiency in spoken English; capacity to provide informed consent. Exclusion criteria are: Primary diagnosis of a functional psychosis; insufficient degree of literacy, comprehension or attention to be able to engage in trial therapy and assessments; currently engaged in a specific programme of psychological treatment for personality disorder or likely to start such treatment during the trial period; currently enrolled in any other trial. Suitable participants are randomly allocated to PEPS therapy plus treatment as usual (TAU) or TAU only. We aim to recruit 340 men and women. The primary outcome is social functioning as measured by the SFQ. A reduction (i.e., an improvement) of 2 points or more on the SFQ at follow-up 72 weeks post-randomisation is our pre-specified index of clinically significant change. Secondary outcomes include a reduction of unscheduled service usage and an increase in scheduled service usage; improved quality of life; and a reduction in mental distress.

**Discussion:**

PEPS therapy has potential as an economical, accessible, and acceptable intervention for people with personality disorder. The results from this randomised controlled trial will tell us if PEPS therapy is effective and cost-effective. If so, then it will be a useful treatment for inclusion in a broader menu of treatment options for this group of service users.

**Trial Registration:**

International Standard Randomised Controlled Trial Number - ISRCTN70660936

## Background

Personality disorder (PD) is a prevalent mental disorder, affecting over 4% of the general population [1]. People with personality disorder suffer high levels of distress, suicide, self-harm, addiction, family breakdown, and social exclusion. Rendu et al. [2] assessed the costs of treating people with PD in primary care as £3,094 per annum, almost twice the costs of people without PD. A prevalence of PD of almost 5% equates to around 3 million people in the UK, costing around £40 million per annum extra to regular care in primary care alone (at 2002 costs). Furthermore, people with PD place considerable demands upon a range of services, including emergency departments, social services, and the criminal justice system. For those who enter outpatient specialist mental health services, treatment costs are around £135 per treatment session [3], and treatment for people with PD is often of long duration. People with PD who offend may enter medium secure services, where the cost is around £176,000 per person per year [3]. If a relatively brief and effective treatment can be offered to a broad spectrum of people with PD dwelling in the community, this will have the potential to improve the lives of people with PD, improve access to services, and also reduce health and non-health service costs.

Systematic reviews of outcomes of psychological treatments for people with PD [4-7] have identified few randomised controlled trials (RCTs). The majority of these studies are underpowered, most have multiple outcome measures, and only about one-third measure social functioning, which is agreed to be the most significant clinical problem for this group of patients. We plan to conduct a well-designed and adequately-powered study of one promising intervention, namely psycho-education combined with problem solving (PEPS) therapy, which has become a popular way of working. Enthusiasm for its use does not obviate the need for a rigorous evaluation of the effectiveness of PEPS therapy; indeed, if it is widely used then evidence of effectiveness - or otherwise - is crucial.

Social problem solving is the process by which an individual attempts to identify or discover solutions to specific problems encountered in everyday living [8]. Good social problem solving skills help people to cope with life's stressors, particularly those with an interpersonal component [9]. Impairment in social functioning is a key component of PD [10-12], hence the emphasis on social functioning that underpins problem solving therapy is highly relevant to the treatment of PD. Using the Social Problem Solving Inventory-Revised (SPSI-R) [13], we have found that people with PD, both community adults presenting for treatment and detained offenders with PD, report greater impairment on all SPSI-R scales compared to a sample of mature students [9]. This information suggests that social problem solving therapy may benefit people with PD.

Meta-analyses have shown problem solving therapy to be effective in improving a range of mental and physical health problems [14-16]. This therapy has not been evaluated with people with PD, nonetheless it is suited to this group because the focus is upon improving social functioning and reducing personal distress. These outcomes are considered to be of paramount importance in the treatment of PD [17]. Furthermore, the aim in therapy is to help people recognise both their strengths and limitations and work with these to learn new skills that will enable them to cope more effectively with life's problems. People with PD have different trait profiles and different problem solving deficits [18], and problem solving therapy is sufficiently flexible to accommodate these differences. It helps clients to adopt a more realistically positive orientation to problem solving, cope better with the negative emotions that hinder effective problem solving, develop a positive problem orientation, and adopt a rational problem solving style that will lead to outcomes that improve social functioning and reduce distress.

Engaging people with PD in treatment is a major challenge [19,20]. The social problem solving approach enhances engagement by offering an accessible framework for change (i.e., the approach appeals to common sense), supporting people in the experience of successful problem solving (i.e., increasing the likelihood of reinforcement of the developing skills), and encouraging independence rather than reliance on therapy (i.e., promoting self-efficacy). Furthermore, PEPS therapy has a preliminary psycho-education component which aims to educate, build rapport, and motivate people for problem solving therapy [21]. Personality disorders and their impact are discussed in a collaborative dialogue and problems that may be worked upon in group sessions are identified.

PEPS therapy has been evaluated with community adults with PD in a Phase 2 exploratory trial [22]. At the end of treatment, compared to a wait-list control group, those treated with PEPS therapy showed better social functioning, as measured by the Social Functioning Questionnaire [23]. All aspects of social problem solving improved over the course of PEPS therapy, and, after controlling for baseline level of social functioning, the most important predictor of improvement in social functioning was a reduction in negative problem orientation, i.e., people felt less threatened by problems and more confident in their ability to solve them [24].

This exploratory study has been identified as important in four ways [25,26]. First, the intervention was brief and hence is likely to be more acceptable to many patients than lengthier interventions; this decreases the likelihood of drop-out and may also be more acceptable to services with limited resources. Second, PEPS therapy was delivered in clinical settings, hence its likely effectiveness in everyday practice was indicated. Third, PEPS therapy was offered to people with any PD or combination of PDs, so it was inclusive rather than exclusive. Fourth, PEPS therapy was delivered by non-specialist staff, hence it would be possible to deliver it relatively cheaply.

Overall, PEPS therapy has the potential to contribute to the UK National Health Service's (NHS) QUIPP agenda (Quality, Improvement, Productivity and Prevention): it is a brief, innovative intervention in which staff can easily be trained and which could be made widely available to people with personality disorder at a stage where prevention of deterioration is possible. However, a definitive evaluation now needs to be conducted. A trial will permit investigation of aspects of the therapy about which there is currently no information. First, a longer-term follow-up is necessary to provide information about the sustainability of gains made during treatment. Second, a cost-effectiveness evaluation of the intervention is required. Third, there is a need to gather information about the respective contributions of psycho-education and social problem solving therapy. We are now conducting a Phase 3 definitive randomised controlled trial to consolidate and extend our knowledge about the effectiveness of PEPS therapy for people with personality disorder (see http://www.peps-trial.co.uk). If improvements in social functioning can be definitively shown to result from therapy and be sustained over time (72 weeks post-randomisation), then this relatively brief intervention could be used more widely across the NHS.

### Study Aims

1. To conduct a randomised controlled trial to evaluate the effectiveness of PEPS therapy compared with treatment as usual in improving social functioning in community adults with personality disorder.

2. To assess the costs and cost-effectiveness of PEPS therapy compared with treatment as usual.

3. To examine intermediate change, specifically the impact of psycho-education on the therapeutic relationship, and the impact of social problem solving therapy on social problem solving skills.

5. To conduct a qualitative investigation of the application of PEPS therapy in practice to identify the views of participants.

### Study Hypotheses

Our primary hypothesis is that, compared with those in treatment-as-usual, those in PEPS therapy will show a greater improvement in social functioning post-therapy and at follow-up 72 weeks post-randomisation. Secondary hypotheses are that, compared with those in treatment-as-usual, those in PEPS therapy will show the following changes both immediately after therapy and at follow-up: (a) a greater reduction in receipt of unscheduled services; (b) a greater increase in receipt of scheduled services; (c) a greater improvement in quality of life; (d) a greater improvement in referrers' ratings of functioning; (e) a greater reduction in anxiety and depression; and (f) improvement on client-ratings of self-identified three key problems. Regarding intermediate changes, we hypothesise that, compared with those in treatment-as-usual, those in PEPS therapy will show: (a) better therapist alliance after psycho-education; and (b) a greater improvement in social problem solving at end of therapy. We also expect PEPS therapy to show an acceptable level of cost-effectiveness, based on thresholds that appear to guide National Institute for Clinical Excellence (NICE) recommendations.

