### Participants

The target population is community-dwelling adults with one or more PD diagnoses, as identified by the International Personality Disorder Examination [27]. Inclusion criteria are: Living in the community (including residential or supported care settings); presence of one or more personality disorder; aged 18 or over; proficiency in spoken English, assessed if necessary by the Basic Skills Agency 'Fast Track 20 Questions' [28]; capacity to provide informed consent. Exclusion criteria are: Primary diagnosis of functional psychosis; insufficient degree of literacy, comprehension or attention to be able to engage in trial therapy and assessments; currently engaged in a specific programme of psychological treatment for personality disorder or likely to start such treatment during the trial period; currently enrolled in any other trial.

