### Interventions

Psycho-education combined with problem solving (PEPS) therapy is a complex cognitive-behavioural intervention that integrates individual and group therapies. Psycho-education is an individual 4-session collaborative dialogue designed to build a rapport with patients, inform them about their personality disorder, discuss its effects on interpersonal relationships and social functioning, and enhance motivation for therapy [21]. In psycho-education, participants are taken through their personality disorder diagnoses, as identified via a structured clinical assessment. Participants are asked what problems they experience in relation to their personality disorder and they are then guided to specify problems which are then prioritised to be addressed in the problem solving therapy sessions.

Problem solving therapy is a 12-session group intervention designed to teach people strategies for solving interpersonal problems [9]. Participants are encouraged to learn the process of a) identifying negative feelings and using these as a cue for initiating the problem solving process; b) defining their problem clearly and accurately; c) setting specific goals for change; d) generating solution options; e) considering the consequences of each option; and f) selecting potentially effective options and organising these into a means-end action plan. Participants are then expected to implement the action plan and are offered individual support sessions to help with implementation. Progress with the action plan is reviewed in the next group session.

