##### Treatment alliance

(Working Alliance Inventory; WAI) [35]. The WAI examines the development of treatment alliance, and will be used to assess the effectiveness of the psycho-education component in developing treatment alliance. The WAI is a 36-item questionnaire that can be administered to both clients and therapists. Each item is rated on a 7-point scale and scores are produced on three factors: the therapeutic bond, the agreement on goals, and the agreement on tasks.

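### Intermediate hypothesis (a) sets therapist alliance after psycho-education against TAU, but psycho-education and its therapist exist only in the PEPS arm, so this is not a valid randomised test

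*Protocol article*

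**What the plan says.** All places are in the protocol article.

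- **Study Hypotheses** words the alliance hypothesis as a between-arm contrast: relative to TAU, "those in PEPS therapy will show: (a) better therapist alliance after psycho-education". Hypothesis (b), on social problem solving at end of therapy, sits under the same comparison.
- **Abstract, Methods** gives the arms: "Suitable participants are randomly allocated to PEPS therapy plus treatment as usual (TAU) or TAU only".
- **Interventions** describes psycho-education only as part of PEPS: "Psycho-education is an individual 4-session collaborative dialogue designed to build a rapport with patients".
- **Treatment alliance** says that the WAI "will be used to assess the effectiveness of the psycho-education component in developing treatment alliance". It adds: "The WAI is a 36-item questionnaire that can be administered to both clients and therapists". It names no TAU clinician to be rated and no TAU time point.
- **Study Aims**, aim 3, asks what psycho-education does to the therapeutic relationship. It mentions no comparison with TAU, whereas aims 1 and 2 do.
- **Participants** excludes anyone "currently engaged in a specific programme of psychological treatment for personality disorder or likely to start such treatment during the trial period".
- **Background** says of the planned trial that "there is a need to gather information about the respective contributions of psycho-education and social problem solving therapy".

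**The concern.** A randomised comparison needs the outcome to be defined in the same way, and at a comparable time, in both arms. Alliance with the psycho-education therapist once those sessions have ended is defined only where those sessions are given. Followed literally, hypothesis (a) leads to one of two results. Either there is no between-arm test, or PEPS participants' ratings of their trial therapist are set against TAU participants' ratings of someone else. The second could be reported with the authority of a randomised comparison although randomisation does not support it.

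A related point is the interest in what each component contributes. PEPS is allocated as a package, so no contrast between the two arms can separate psycho-education from problem solving therapy.

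**Working it through.** The article gives no figure for the alliance hypothesis, so the check sets the text side by side.

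1. **Is the outcome defined in both arms?** Hypothesis (a) needs a therapist and a moment after psycho-education. The PEPS arm has both: four individual sessions, then the group therapy. The TAU-only arm has neither. That TAU participants have no trial therapist is inferred from the allocation; the article does not say it in so many words.

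2. **Does another section supply the TAU counterpart?** Treatment alliance describes the WAI by its three factors (bond, goals, tasks) and its raters (clients and therapists), and ties it to the psycho-education component. Aim 3 does the same. Analyses specifies between-arm comparisons for the primary and secondary outcomes; the WAI is listed separately under Intermediate outcomes, and no between-arm analysis of it is given. The TAU contrast for alliance therefore appears only in Study Hypotheses.

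3. **Could a usual-care rating stand in?** Let *p* be the share of TAU participants with a professional they could rate. The article does not state *p*, so take the full range from 0 to 1. With 170 recruited per arm, the number of possible TAU ratings is 170 × *p*, between 0 and 170.
   - At *p* = 0 there are no control data.
   - At 0 < *p* < 1 the TAU ratings come from those with such contact after randomisation. The compared groups are then no longer the randomised groups.
   - At *p* = 1 the selection problem goes, but the arms still rate different things: a new therapy relationship after four sessions, against a usual-care contact of unspecified type and length.

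   At no value of *p* does the contrast isolate psycho-education.

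4. **Does the same problem affect hypothesis (b)?** No. The SPSI-R is a 25-item client self-report of problem solving skills. It needs no therapist and can be completed in both arms.

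5. **Is the sample size affected?** No. It is set for the Social Functioning Questionnaire (SFQ): 2 × 4.53² × (2.576 + 0.842)² / 2² ≈ 120 per arm, as stated (power 80.1%). For dropout, 120 / 0.70 = 171.4, close to the stated 170. None of this depends on the WAI.

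**The case against.** The strongest case on the other side has four parts.

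**TAU is not an absence of care.** The exclusion covers only a specific psychological programme for personality disorder. Recruitment describes referrals through mental health services and community teams, a referrer rates the GAF, and Analyses plans to describe which service or professional treated what under TAU. This stands. A reader might infer that most TAU participants have nobody to rate; the article does not support that. Nor should the fact that 0 of 170 TAU participants have an alliance after psycho-education be read as a measure of missing WAI data. It is true by definition of the arm.

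**The schedule may be elsewhere.** Figure 2 and the full protocol are not shown and may say who is rated in TAU and when. This too stands as far as it goes, so it would be wrong to assert that no TAU rating is planned. But the point does not rest on missing detail. A scheduled TAU rating would still concern another relationship and would still depend on having such contact.

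**The hypothesis may be meant loosely.** Aim 3 and Treatment alliance already read as a process question, and no between-arm test of the WAI is specified. That supports the remedy: the hypothesis should match those sections.

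**Background does not promise component effects.** A reader might infer a claim that PEPS against TAU will isolate each component's contribution. The sentence speaks only of a need to gather information, and the WAI and SPSI-R do gather some. A clarifying statement is enough.

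**Conclusion.** The point holds in a limited form. Hypothesis (a) is stated as a PEPS-versus-TAU comparison of something that, as worded, exists only in the PEPS arm, and the article's own aim and instrument description carry no such contrast. Ratings of usual-care professionals in TAU are possible, but they would not turn the contrast into a valid randomised test of psycho-education.

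The reach is narrow: one of two intermediate hypotheses. The primary SFQ outcome, the sample size, the secondary outcomes and the SPSI-R comparison are untouched, and no numerical result of the plan changes.

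The conclusion assumes that TAU-only participants receive no psycho-education and have no trial therapist, as the allocation and Interventions imply. It needs no assumption about how many TAU participants have a professional to rate.

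**What to change.** - In Study Hypotheses, remove the comparison with TAU for the WAI. Restate (a) as a description of alliance within the PEPS arm after psycho-education, labelled non-randomised.
- If WAI ratings are collected in TAU, name the relationship and the time point rated, and report them descriptively, not as a randomised comparison.
- Keep hypothesis (b) as a between-arm comparison on the SPSI-R.
- State that the WAI and SPSI-R give process information on the two components but do not separate their effects.

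Relating alliance to later attendance or to SFQ at 72 weeks would be an optional exploratory addition and is not needed to cure the wording.

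The cost is a change of wording, with no new data. The downside is that the alliance result becomes exploratory and can no longer be presented as a between-arm effect.

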## Method

### Design

This is a pragmatic, two-arm, multi-centre, parallel, randomised controlled clinical trial.

### Ethics

Approval for the research was given by the South East Wales Research Ethics Committee - Panel C (Ref: 09/WSE03/48) and from the Research and Development (R&D) departments of the participating NHS Trusts: Central and North West London NHS Foundation Trust (24195/LNW); Cwm Taf Health Board (CT/039/09); Tees, Esk and Wear Valleys NHS Foundation Trust (24195/CDTV).

### Participants

The target population is community-dwelling adults with one or more PD diagnoses, as identified by the International Personality Disorder Examination [27]. Inclusion criteria are: Living in the community (including residential or supported care settings); presence of one or more personality disorder; aged 18 or over; proficiency in spoken English, assessed if necessary by the Basic Skills Agency 'Fast Track 20 Questions' [28]; capacity to provide informed consent. Exclusion criteria are: Primary diagnosis of functional psychosis; insufficient degree of literacy, comprehension or attention to be able to engage in trial therapy and assessments; currently engaged in a specific programme of psychological treatment for personality disorder or likely to start such treatment during the trial period; currently enrolled in any other trial.

